**FIGURE 1 F1:**
[figure not shown]
ASMA-D study schematic diagram.

**FIGURE 2 F2:**
[figure not shown]
SPIRIT flow diagram of the ASMA-D trial.

### 2.2. Eligibility criteria

The inclusion criteria are as follows: (1) Adults between the ages of 19 and 65; (2) Those diagnosed with mild to moderate MDD in an expert interview evaluation according to the DSM-V diagnostic criteria [Score of 7–24 on the Hamilton Rating Scale for Depression (HAM-D)]; (3) Those on stable medication for 28 days prior to study participation; and (4) Those who provide informed consent and voluntary participation.

The exclusion criteria are as follows: (1) Difficulty using smart phones or inability to independently use the App; (2) A diagnosis of severe MDD in an expert interview evaluation according to the DSM-5 diagnostic criteria (score of 25 or more on HAM-D); (3) Severe mental disorders (current or in the past), including MDD with psychotic features, bipolar affective disorder, personality disorder, obsessive compulsive disorder, autism spectrum disorder, and substance use disorder; (4) History of brain injury, epileptic seizures, intellectual disability, or cognitive disorders; (5) History of severe physical disorders, including cancer, tuberculosis, severe cardiovascular disease, etc.; and (6) Individuals participating in other cognitive behavioral therapies or activities related to stress relief.

### 2.3. Generic description of the App

The App implements mobile-based strategies for stress relief that can be used on most Android and iOS-based mobile devices. The stress relief strategies involve three modules: meditation, the cognitive approach, and relaxation sounds. Additionally, the App includes a module for objective stress monitoring. The App was originally designed and developed in Korean, but English, Chinese, and Japanese versions are also available. For use in the treatment environment, the manufacturer also provides a service that allows therapists to check their patients’ application usage and their stress level measured by the stress monitoring module. The general user interface of the App is shown in the screenshot in Figure 3. The specific user interface and contents for each module are described below.

**FIGURE 3 F3:**
[figure not shown]
Screenshots of the App user interface. All participants log in with their ID and password on the log-in page **(A)**. Participants can watch a tutorial about application use at any time **(B)**. The Home screen recommends treatment programs based on the results of participants’ recent objective stress monitoring, and participants can access the desired content from the menu bar **(C)**. Participants can also directly access content by category through the side menu **(D)**.

#### 2.3.1. Meditation module

The meditation module in the App is modified to be mobile and self-utilizing based on the MBSR program created by Jon Kabat-Zinn et al. (37). The meditation module consists of two components: “two weeks course for meditation” and “meditation and breathing.” The “two weeks course for meditation” contains 14 topics related to MBSR, and provides 5–15 min with backgrounds and voices that can help stabilize the mind and focus (Table 1 and Figure 4). It helps participants gain a better understanding of MBSR and learn how to train in “meditation and breathing.” There are nine topics (four training topics centered on breathing methods and five topics centered on meditation) in the “meditation and breathing” component, provided in both long (15 min or longer) and short (less than 10 min) forms, with backgrounds and voices that can help stabilize the mind and focus (Table 1 and Figure 4). Therefore, participants can utilize the content from relevant topics according to their situation.

**TABLE 1 T1:** Titles and contents of the meditation module.

Component	Title
Two weeks course for meditation	Prolog, before entering the meditation, introduction
	DAY 1- Self-regulation
	DAY 2- Feel the nature through breathing
	DAY 3- Come back to your breath at any time
	DAY 4- Relaxation by focusing on the object
	DAY 5- Image training, the power of imagination
	DAY 6- Come back to here and now through breathing
	DAY 7- Observation of thoughts and emotions, returning to the here and now
	DAY 8- Observation of the senses, returning to the here and now
	DAY 9- Mindfulness yoga, Follow your mind through movement
	DAY 10- Awakening nature through eating
	DAY 11- Walking meditation, meditating while walking
	DAY 12- Loving kindness meditation, warm mindfulness
	In closing, what kind of meditation is appropriate for me?
Meditation and breathing	Meditation 1–Loving-kindness meditation, getting closer to yourself through the change of feelings you feel while thinking about charity
	Meditation 2–Self-compassion meditation, recognizing the connection between you and the world and being kind to yourself
	Meditation 3–Compassion meditation, cultivate one’s own mind through supporting compassionate objects
	Meditation 4–Guided image method- Forest, imagining walking in the forest to relax and recharge the mind
	Meditation 5–Guided image method- Sea, imaging relaxation and recharging the mind through imagining walking on the sea
	Breathing 1–Mindful breathing method 1, the sensations felt in my body and the changes that occur in my body through breathing
	Breathing 2–Mindful breathing method 2, through breathing, the sensations felt in my body and body tension are relieved and my mind is relaxed
	Breathing 3–Body-awareness breathing method 1, relaxation through awareness of my whole-body senses
	Breathing 4–Body-awareness breathing method 1, improving attention through awareness of my whole-body senses

**FIGURE 4 F4:**
[figure not shown]
Screenshots of the meditation module. This module has two parts (**A**: “Two weeks course of meditation” and **B**: “Meditation and breathing”), wherein participants select one of several choices presented as a list and listen to the guided audio recording. The content was presented in Korean, but the examples in this figure are presented in English to aid understanding for international readers.

#### 2.3.2. Cognitive approach module

The cognitive approach module consists of two components, “emotional diary” and “ee-Think.” In “emotional diary,” participants can express their feelings through emojis and journaling (Figure 5A). The transactional theory of stress suggests that keeping a diary can help manage stress through re-formulating one’s own situation-related stress experience (39, 40). Therefore, the “emotional diary” component can help participants manage their stress through keeping an emotional diary.

**FIGURE 5 F5:**
[figure not shown]
Screenshots of the cognitive approach module. The module includes two parts (**A**: “Emoji and Emotion Diary” and **B**: “Re-Think”). Emoji is a tool for expressing varied emotions; the participant can choose what is presented as a sample or create their own Emoji by selecting a color or shape such as eyes and mouth (A-1). The diary is created by checking the emotional intensity related to the previously created Emoji through the slider and entering the title and details (A-2). Participants can see the content of their diary and the emoji of any particular day through the calendar (A-3). In all steps in the “Re-Think” part, participants write answers to the questions displayed on the screen (B-2), and select emotion cards (B-3). The content was presented in Korean, but the examples in this figure are presented in English to aid understanding for international readers.

The “re-think” component aims to help participants practice changing their negative thoughts into positive ones by highlighting the inter-relationships between thoughts, feelings, physical sensations, and behaviors and dealing with biased thinking that induces negative emotions (19–21). The “re-think” component consists of three steps (Figure 5B). First, participants express their concerns that cause them stress, in detail. Second, they compare the expressed emotions and concerns, and then try to see the actual situation rather than the related emotions. Third, participants advise themselves from a third-person perspective based on the contents expressed up to the previous point. Then, participants are guided to think about the change of emotions about their concerns from the starting point through the previous steps and put it in writing.

#### 2.3.3. Relaxation sound module

This component involves two types of sounds: the sounds found in the natural environment (Sound Therapy) and those associated with Autonomous Sensory Meridian Response (ASMR), known to help recover from stress (41). Since there is no consensus on which type and delivery of sound is effective, this category tries to provide a wide range of experiences to help participants choose the sound they prefer. To suit the various personal preferences, the manufacturer provides 117 sounds recorded in 3 places (Jeju Island, The Republic of Korea; Okinawa, Japan; and Hawaii, USA) in the Sound Therapy component and 30 sounds in ASMR. Figure 6 presents a screenshot of the user interface of this module, with each component.

**FIGURE 6 F6:**
[figure not shown]
Screenshots of the relaxation sound module. The module includes two types of sounds (**A**: “Sound Therapy” and **B**: “ASMR”). Participants can select a region of natural scenery they would like to hear and chose from the curated “Sound therapy” list (A-1). Various types of videos are prepared for each region, and participants can select from them (A-2). Panel (A-3) shows the video playback screen. Participants can click the video they want from the list presented in the ASMR component (B-1). Panel (B-2) shows the screen where the video is played in “ASMR.” Both “Sound Therapy” and “ASMR” can be accessed as a list from the playback screen (B-3). The content was presented in Korean, but the examples in this figure are presented in English to aid understanding for international readers.

#### 2.3.4. Objective stress monitoring

For the objective measurement of stress, heart rate variability (HRV), that reflects stress response *via* ANS activity, can be measured by acquiring the photoplethysmography (PPG) through a mobile camera (42). To record the pulsatile PPG signal and calculate intervals between R-peak (RR intervals) intervals (R-peak interval), the module built into the App was designed for each phone based on the algorithm of a previous study (43), that showed relative high performance (relative errors < 5%, Pearson correlation > 0.9, and standard estimated error < 5 beats-per-minutes) with reference to a medical device (Beurer BC 08, Beurer GmbH, Germany). The App instructs all participants not to speak and make any movement during a 1-min recording with visual guidance (Figure 7).

**FIGURE 7 F7:**
[figure not shown]
Screenshots of the objective stress monitoring. The “Guide” shows how to measure PPG and guides participants on situations to pay attention to during PPG measurement **(A)**. When the measurement starts, the measured pulse rate is displayed on the screen, and the progress is displayed in a circle to check that 1 min has elapsed **(B)**. When the measurement is completed, autonomic nervous balance, autonomic nervous activity, heart rate variability, and stress index are displayed based on the results **(C)**. Participants can see the change in their results on the result screen and check the interpretation of the results **(D)**. The content was presented in Korean, but the examples in this figure are presented in English to aid understanding for international readers.

Continuous HR signals are normalized to unit variance and then power spectra were determined using the Welch periodogram method (44). Total power in the frequency range (TP: 0–0.40 Hz) is divided into low frequency (LF: 0.04–0.15 Hz) and high frequency (HF: 0.15–0.40 Hz) (45). The TP, LF, and HF components are calculated in normalized units. TP is interpreted as autonomic nervous activity, and LF/HF reflects autonomic nervous balance. In addition, HRV is calculated by obtaining a histogram for each heartbeat time interval and dividing the total frequency by the maximum of the density distribution (46). The results show autonomic nervous activity, autonomic nervous balance, and HRV (Figure 7). To help participants interpret their results, the manufacturer has developed a stress index that converts the sympathetic nerve activation level into a score between 0 and 100, with a higher score indicating higher stress.

### 2.4. Setting

Three university hospitals in Republic of Korea participating in the study will recruit patients with depression to use the App. The Korea University Guro Hospital and Korea University Anam Hospital are in the inner center of the Capital, and Korea University Ansan Hospital is in Ansan city, on the outskirts of the capital area. Each hospital is a general hospital, and the Korea University Guro Hospital will lead the ASMA-D study. For patient recruitment, 96 patients (48 interventions and 48 controls) in the Korea University Guro Hospital, and 60 patients (30 interventions and 30 controls) each from Korea University Anam Hospital and Korea University Ansan Hospital are expected.

Candidates participating in the current study can use the “inMind” application free of charge. During the 8-week study period, participants will be provided with transportation expenses worth KRW 10,000 for every 2-week hospital visit. In addition, participants who complete 22 days or more out of 24 days (excluding holidays) according to the planned schedule without interruption or dropout during the 4-week inMind usage period will receive a monetary reward worth KRW 100,000.

### 2.5. Recruitment process and screening for enrollment

Patients with depression who visit the hospital and are interested in the advertisements posted in the participating hospitals will be screened. Once interested patients contact the research team, they will be screened for eligibility by the psychiatrist according to the above-described criteria. After eligibility is established, information regarding the study will be given to the prospective participants. Once the patient agrees to participate, informed consent will be acquired, and randomization will occur only after the participant is enrolled.

### 2.6. Randomization

Eligible volunteers will be randomly assigned to the fAPP or dAPP groups. Randomization is conducted using block randomization by each clinical center. To prevent bias toward one treatment group, eight patients will be configured in blocks and will be randomly assigned to the fAPP and dAPP groups within each block. For consistent allocation, randomization will be done using a pre-built program. This program is created by Korea University Guro Hospital to blind the researcher from assignment information in advance. The allocation sequence was prepared by researchers who did not participate in this protocol, and was used in the pre-built program. Researchers at each institution can conceal the sequence through the issued ID and password, and the process remains in a log.

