### 2.7. Interventions

#### 2.7.1. Administration of the App

Participants will be instructed to use the App autonomously for 4 weeks at home, in addition to their usual treatment, during the period of using the App (T1 for fAPP group, T2 for dAPP group). According to their assigned group, each participant will receive basic instructions from the researcher on how to use the App.

As the purpose of using the App is to obtain an additional stress relief effect in the usual treatment for patients with depression, the schedule for the App will not be strictly controlled; the researchers will provide a 4-week schedule as a guideline to ensure the use of more than the minimal. As a minimum standard for usage, the schedule will guide participants to use the components of each module at least once a day, 6 days a week or more, and the use of additional content is left to the participant’s discretion. However, regarding the meditation module, the participants will be guided to conduct training after completing psychoeducation in consideration of the characteristics of the content. The App has implemented a system that alerts the user twice per day at a time they select if it is not utilized at least once per day. The researcher will help participants who have provided permission to activate the alarm system in the App. However, whether a participant follows these guidelines is not a determining factor in excluding respective participants’ data.

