### 2.12. Sample size and power calculations

To the best of our knowledge, there are no studies on stress-reduction programs for depression patients using a mobile application; hence, we have assumed the sample size based on the effect size of 0.28, being half of the effect size of 0.56 reported in a previous study that applied MBSR in patients with depression (59). For all patients with depression, the change in DASS-21 score from pre- to post-administration of the App would be analyzed using analysis of variance for a 2 × 2 crossover design (60). As we have assumed no carry-over effects, this was not considered in calculating the sample size. Sample size calculations were conducted using the statistical software G * Power 3.1.9.2 (61). The minimum sample was identified as 172 (fAPP = 86, dAPP = 86) based on an estimated between-group effect on post-intervention stress outcomes between the fAPP and dAPP with a power of 0.95 and an alpha of 0.05. Therefore, the current study will enroll 215 participants and allow for up to a 20% loss to follow-up, expecting a minimum effective sample size of 172 individuals.

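### A fixed block of eight within each centre lets anyone there who tracks past allocations deduce about 19% of assignments with certainty, although the list itself is concealed

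*Protocol article*

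**What the plan says.** Section 2.6 stratifies the allocation by site: "Randomization is conducted using block randomization by each clinical center". It then gives one block size, with no variation: "eight patients will be configured in blocks and will be randomly assigned to the fAPP and dAPP groups within each block". The same section describes the concealment measures. People outside the protocol prepared the sequence, a purpose-built program holds it, access needs an issued ID and password, and use is logged.

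Section 2.1 makes the trial single-blind: outcome assessment is blinded and participants know their group. Section 2.7.1 has a researcher brief participants according to group: "each participant will receive basic instructions from the researcher on how to use the App". For enrolment, section 2.5 says of interested patients that "they will be screened for eligibility by the psychiatrist", and randomisation follows only after consent and enrolment.

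Section 2.4 gives the planned centre sizes. At the lead site it expects "96 patients (48 interventions and 48 controls) in the Korea University Guro Hospital". Each of the remaining two sites is to contribute 60, split equally between the arms.

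**The concern.** The password and program hide the list of future assignments. They do not hide what has already happened. One group starts the App at once and the other waits 28 days, so each allocation is visible at the site from the start. Once four patients in a block have gone to one group, every remaining place in that block belongs to the other. The last place in each block can always be deduced.

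Randomising only after enrolment does not remove this, because a forced assignment can be known before the next patient is screened. Eligibility involves some judgement (a diagnostic interview, a HAM-D range, the ability to use the App unaided), and the timing of enrolment is flexible. If the person deciding on enrolment could foresee the next group, that could influence who enters it. Section 2.13 adjusts for baseline differences that are found, but this would not correct for unmeasured traits such as motivation.

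**Working it through.** The protocol gives no predictability figure of its own, so there is none to reproduce.

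**Inputs**
- Block size 8, fixed, within centre (section 2.6).
- Equal arms. Section 2.12 states: "The minimum sample was identified as 172 (fAPP = 86, dAPP = 86"; section 2.4 plans 48/48 and 30/30. The split of 4 and 4 within a block is inferred from this.
- Centre sizes 96, 60 and 60 (section 2.4), total 216. Section 2.12 gives 215; the difference is immaterial here.

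**Forced assignments in one block.** There are C(8,4) = 70 equally likely balanced blocks. An assignment is forced once one arm has used its four places.

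| Forced at end of block | Number of blocks |
|---|---|
| 1 | 40 |
| 2 | 20 |
| 3 | 8 |
| 4 | 2 |

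Mean = (40×1 + 20×2 + 8×3 + 2×4)/70 = 112/70 = 1.6, which is 20% of 8. The closed form for a block of 2m agrees: 2m/(m+1) = 8/5 = 1.6 with m = 4.

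**By centre**
- 96 patients: 12 complete blocks, 12 × 1.6 = 19.2 (20.0%).
- 60 patients: 7 complete blocks and half a block. None of the first four places in a block can be forced, so 7 × 1.6 = 11.2 (18.7%).
- All centres: 19.2 + 11.2 + 11.2 = 41.6 of 216 = 19.3%.

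**Best-guess accuracy.** Always guessing the arm that is behind is right, on average, m + (4^m/C(2m,m) − 1)/2 = 4 + (256/70 − 1)/2 = 5.33 times in 8, or 66.6%, against 50% by chance.

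**Effect of mixed block sizes.** Lists were simulated for an observer who knows the set of sizes but not the size of each block, and who updates the odds after every allocation.

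| List | Patients | Known with certainty | Best guess correct |
|---|---|---|---|
| Fixed 8 | 60 | 18.6% | 66.1% |
| Mixed 6/8/10 | 60 | 1.6% to 1.8% across runs | 66.0% |
| Mixed 8/10/12 | 60 | 1.4% | 64.6% |
| Fixed 8 | 96 | 20.0% | not computed |
| Mixed 6/8/10 | 96 | 1.6% | not computed |

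Mixing 6, 8 and 10 removes nearly all certainty but does not improve the odds of a good guess.

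**The case against.** **Who sees the allocations.** A reader might infer that the staff who enrol patients see every past allocation. The protocol does not say so. A psychiatrist screens (section 2.5) and a researcher instructs (section 2.7.1); whether they are the same person is not stated. HAM-D is both an eligibility criterion and a clinician-rated outcome. If the same clinicians do both, the blinding in section 2.1 should keep past allocations from them. This objection stands, and the point is limited accordingly.

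**Deducible is not the same as known.** A reader might also infer that one assignment in five is in fact known beforehand. The 19% is a ceiling. It applies to someone who knows the block size, knows where blocks begin and misses no case. This also stands.

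**The crossover design.** A third tempting inference is that any selection bias would be beyond repair. Every participant receives both conditions, and section 2.12 names a 2 × 2 crossover analysis. Stable differences between patients cancel in that contrast, so selection would bias it only by sorting patients on how they change between periods. The incentive to steer is also weaker, since everyone gets the App within eight weeks. What remains is the period-1 comparison: section 2.12 bases its sample size on an estimated between-group effect on post-intervention stress, and there the composition of each group matters. That DASS-21 is an unblinded self-report is a separate matter and does not add to selection bias.

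**The remedy's limits.** Best-guess accuracy hardly moves, the sequence already exists, and a published block size cannot be withdrawn. All three are correct. They limit the gain to removing certainty for patients not yet randomised.

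**Conclusion.** The point holds as a modest design weakness. With a fixed block of 8 within each centre and allocation open at the site, 41.6 of 216 assignments (19.3%) can be deduced with certainty by anyone who knows the block size and tracks the sequence. Concealing the list does not prevent this. The figure assumes a 4 and 4 split in each block and the planned centre sizes. Whether anyone who decides on enrolment is in that position is not stated, and nothing in the document shows that selection would occur. The exposure lies mainly in the period-1 between-group comparison. The within-patient contrast is largely protected, provided patients are not sorted on how they will change over time.

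**What to change.** For the part of each centre's list not yet used, have the list preparer regenerate the sequence with randomly mixed block sizes, for example 6, 8 and 10, and keep the sizes from everyone at the sites. Certain predictions fall from about 19% to about 2%; over 216 patients that would be about 4 (216 × 0.016 to 0.018 = 3.5 to 3.9) instead of 41.6. Fewer benefit if recruitment is already under way.

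The work is one regenerated list per centre in the existing program and one amended sentence in section 2.6. The statistical cost is that the largest possible imbalance at the end of a centre's list rises from 4 to 5 patients.

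If recruitment is complete, no change to the list is possible. The trial report should then state the fixed block size as a limitation and say whether the screening psychiatrists had access to past allocations.
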